## Abstract

**Background:**

Data generated with the body composition monitor (BCM, Fresenius) show, based on bioimpedance technology, that chronic fluid overload in hemodialysis patients is associated with poor survival. However, removing excess fluid by lowering dry weight can be accompanied by intradialytic and postdialytic complications. Here, we aim at testing the hypothesis that, in comparison to conventional hemodialysis, blood volume-monitored regulation of ultrafiltration and dialysate conductivity (UCR) and/or regulation of ultrafiltration and temperature (UTR) will decrease complications when ultrafiltration volumes are systematically increased in fluid-overloaded hemodialysis patients.

**Methods/design:**

BCM measurements yield results on fluid overload (in liters), relative to extracellular water (ECW). In this prospective, multicenter, triple-arm, parallel-group, crossover, randomized, controlled clinical trial, we use BCM measurements, routinely introduced in our three maintenance hemodialysis centers shortly prior to the start of the study, to recruit sixty hemodialysis patients with fluid overload (defined as ≥15% ECW). Patients are randomized 1:1:1 into UCR, UTR and conventional hemodialysis groups. BCM-determined, ‘final’ dry weight is set to normohydration weight −7% of ECW postdialysis, and reached by reducing the previous dry weight, in steps of 0.1 kg per 10 kg body weight, during 12 hemodialysis sessions (one study phase). In case of intradialytic complications, dry weight reduction is decreased, according to a prespecified algorithm. A comparison of intra- and post-dialytic complications among study groups constitutes the primary endpoint. In addition, we will assess relative weight reduction, changes in residual renal function, quality of life measures, and predialysis levels of various laboratory parameters including C-reactive protein, troponin T, and N-terminal pro-B-type natriuretic peptide, before and after the first study phase (secondary outcome parameters).

**Discussion:**

Patients are not requested to revert to their initial degree of fluid overload after each study phase. Therefore, the crossover design of the present study merely serves the purpose of secondary endpoint evaluation, for example to determine patient choice of treatment modality. Previous studies on blood volume monitoring have yielded inconsistent results. Since we include only patients with BCM-determined fluid overload, we expect a benefit for all study participants, due to strict fluid management, which decreases the mortality risk of hemodialysis patients.

**Trial registration:**

ClinicalTrials.gov, NCT01416753

## Background

The importance of volume control has been recognized since the early years of hemodialysis [1], but was previously hampered by the limitations of noninvasive methods used to estimate the hydration state of hemodialysis patients [2]. Recently, the body composition monitor (BCM, Fresenius Medical Care, Bad Homburg, Germany) was introduced, and prescribed to combine a whole-body bioimpedance spectroscopy method with an inbuilt physiologic tissue model [3]. BCM measurements of volume status were successfully validated against gold standard determinations of extracellular and intracellular volume, total body water, fat, fat-free mass and fluid overload [4-7]. Hemodialysis patients with fluid overload >15% extracellular water (ECW), as determined by BCM measurements, were prospectively found to have a markedly higher mortality risk than patients with <15% ECW (hazard ratio (HR) = 2.1, *P* = 0.003) [8]. These results have attracted considerable attention in the dialysis community, and are challenging the concept of interdialytic weight gain (IDWG) as a proxy for fluid retention [9] and measure of nonadherence [10]. By contrast, the novel data imply that reaching the adequate hydration status or ‘dry weight’ postdialysis is more beneficial than reducing fluid intake during the interdialytic interval.

Lowering the dry weight of hemodialysis patients without increasing treatment time can be accompanied by intradialytic complications, mostly cramping and hypotension [11]. Noninvasive hematocrit monitoring technologies, such as crit-line monitoring, were developed as early as 1991 on the basis of optical transmission/optical absorbance [12-15] or ultrasound [16-18] with the ultimate goal to prevent such complications. Determining a hematocrit threshold and manipulating ultrafiltration (UF) rates to maintain the instantaneous hematocrit value two units below the established hematocrit threshold led to a twofold reduction in intradialytic symptoms in hypotension-prone patients [19]. However, various subsequent trials, including the Crit-Line Intradialytic Monitoring Benefit (CLIMB) study [20] failed to yield consistently positive results [21-24], possibly because there is considerable intra- and inter-individual variability of the BVM changes [25].

In the CLIMB study, blood volume monitoring (BVM, for example, crit-line monitoring) was studied as a voluntary adjunct to care, and no algorithms, clinical management advice or instructions were provided for the conventionally monitored patients [20]. However, response options to BVM have been available since the early ’90s [16] and include feedback regulation of ultrafiltration [26] based on stored BVM measurements [27] using fuzzy logic principles [28], and regulation of the dialysate conductivity [29-35]. Feedback control of blood temperature, for example with the body temperature monitor (BTM, Fresenius) [36-38], is an alternative method to prevent intradialytic hypotension.

In the present study, we use BCM measurements to determine a patient’s ideal dry weight and do not use BVM as a diagnostic tool. However, we utilize BVM response options currently available in modern dialysis machines, namely, (1) regulation of ultrafiltration and dialysate conductivity (UCR, Nikkiso Europe GmbH, Hanover, Germany) and (2) regulation of ultrafiltration (Fresenius) in those hemodialysis patients with ≥15% ECW, who are concurrently subjected to systematic increases in ultrafiltration volume, to reach a final dry weight of normohydration weight −7% of ECW. When using the Fresenius machines, we simultaneously employ the BTM to maintain a patient’s original body temperature (hence UTR means ultrafiltration and temperature regulation). Our aim is to assess whether UCR and/or UTR are superior to conventional hemodialysis with respect to frequency of intra- and post-dialytic complications (primary outcome), and improvement of various secondary outcome parameters, possibly related to improved hemodialysis stability and volume status.

## Methods/design

### Hypothesis

In comparison to conventional hemodialysis, regulation of ultrafiltration and dialysate conductivity (UCR) and/or regulation of ultrafiltration and temperature (UTR) will decrease intra- and post-dialytic complications when ultrafiltration volumes are systematically increased in fluid-overloaded hemodialysis patients.

### Objectives and outcome measures

The primary objective is to demonstrate superiority of ultrafiltration and dialysate conductivity regulation (UCR) and/or ultrafiltration and temperature regulation (UTR) over conventional hemodialysis, in preventing intra- and post-dialytic complications, when fluid-overloaded hemodialysis patients receive systematic fluid reduction, to reach a final dry weight of normohydration weight −7% of ECW postdialysis. The primary outcome measure is the total number of hemodialysis sessions per patient that were accompanied, intra- or post-dialytically, by at least one symptom most likely related to fluid withdrawal (as specified in Table1), divided by the number of hemodialysis sessions at risk (as by study protocol: 12 sessions per patient in study phase 1). Both groups, UCR and UTR, will be compared against the conventional hemodialysis group, and afterward against one another, using the two-sided Student’s *t* test

**Table 1 T1:** Complications related to fluid withdrawa

(1)	Intradialytic cramping
(2)	Intradialytic hypotension (>40 mmHg SBP) within 30 minutes: clinically asymptomatic
(3)	Intradialytic hypotension (>40 mmHg SBP) within 30 minutes: clinically symptomatic
(4)	Clinically symptomatic intradialytic hypotension: unspecified drop in SBP
(5)	Unspecified intradialytic complication, most likely related to fluid withdrawal
(6)	Patient-reported postdialysis complication, most likely related to fluid withdrawal

The secondary objectives are:

(a). To demonstrate superiority of ultrafiltration and dialysate conductivity regulation (UCR) and/or ultrafiltration and temperature regulation (UTR) over conventional hemodialysis, in preventing specific intradialytic complications:when fluid-overloaded hemodialysis patients receive systematic fluid reduction, to reach a final dry weight of normohydration weight −7% of ECW postdialysis. The secondary outcome measure for objective (a) is the total number of hemodialysis sessions per patient which were accompanied by the respective symptom most likely related to fluid withdrawal (1 to 6), divided by the number of hemodialysis sessions at risk (as by study protocol: 12 sessions per patient in study phase 1). Both groups, UCR and UTR, will be compared against the conventional hemodialysis group, and afterward against one another, using the two-sided Student’s *t* test.

1. intradialytic cramping

2. clinically asymptomatic, intradialytic hypotension (>40 mmHg drop in systolic blood pressure (SBP) within 30 minutes)

3. clinically symptomatic, intradialytic hypotension (>40 mmHg drop in SBP within 30 minutes)

4. clinically symptomatic, intradialytic hypotension (even if it is not possible to identify a sudden drop in blood pressure, for example, patients may slowly move towards low blood pressure values (f. ex. below 100 mmHg SBP), and report symptoms)

5. unspecified intradialytic symptoms or events, which are most likely related to fluid withdrawal

6. patient-reported postdialysis complication, most likely related to fluid withdrawal (All of the above also listed in Table1)

(b). To demonstrate superiority of UCR and/or UTR over conventional hemodialysis in allowing patients to reach a lower body weight, relative to his/her postdialysis weight at the beginning of study phase 1 (time zero). The secondary outcome measure for objective (b) is the difference in postdialysis body weight from time zero to the end of study phase 1, divided by the postdialysis body weight at time zero.Example: if a patient has a postdialysis body weight of 65 kg at time zero (the last hemodialysis session before the first dry weight reduction), and reaches a postdialysis body weight of 62 kg at the end of the first study phase, his difference in body weight will be 65 kg – 62 kg = 3 kg. Relative to this patient’s postdialysis body weight at time zero, weight reduction from beginning to end of study phase 1 will be 3/65*100 = 4.61%.The relative weight reduction in both groups, UCR and UTR, will be compared against the conventional hemodialysis group, and afterward against one another, using the two-sided Student’s *t* test.

(c). To assess the amount of sodium transferred to the patient or withdrawn from the patient during conventional hemodialysis, UCR and UTR. The amount of sodium removed during hemodialysis is a function of the ultrafiltration volume, the effective diffusion gradient for sodium, and diffusive sodium clearance. The effective diffusion gradient depends on the plasma water - dialysate sodium (DNa) difference, and the Gibbs-Donnan coefficient, the latter being a function of the plasma protein concentration but also being influenced by other ions in the dialysate [39,40]. The assumption that sodium removal by ultrafiltration is equal to the plasma water sodium concentration, multiplied by the ultrafiltration volume, is a simplification [41,42]. Electrolyte balances may also be influenced by the membrane charge [43]. Therefore, the amount of sodium transferred will be measured on the dialysate side. Sodium transfer will be calculated from the difference between the mean sodium concentration in partially collected, used dialysate and the fresh DNa concentration, multiplied by the total amount of dialysate used. Results will be compared to a two-pool sodium model and parameters of the model will be adjusted using the measured transfer data. The above described method is not applicable to the UCR group because the sodium concentration of fresh dialysate is not kept constant during treatment. In order to establish the model, we will measure at least ten patients during three hemodialysis sessions, and due to the formerly stated, we can only use the dialysate from patients in the conventional hemodialysis group and in the UTR group. However, after having established this model, sodium transfer for all patients - conventional, UTR, and UCR - can be calculated using this very model. The amount of sodium transferred to or withdrawn from the patient will be calculated for each patient, according to the model established in the way stated here above. The secondary outcome measure for objective (d), for example, the sodium transferred in both groups, UCR and UTR, will be compared against the conventional hemodialysis group, and afterward against one another, using the two-sided Student’s *t* test.

(d). To assess if stricter volume control by conventional hemodialysis, UCR and/or UTR influences predialysis serum concentrations of (1) C-reactive protein, (2) D-dimer, (3) fibrinogen, (4) troponin T, and (5) N-terminal pro-B-type natriuretic peptide. These proteins are used as read-outs for inflammation (1, 2, 3), coagulation (2, 3), and cardiac function (4, 5) and are routinely determined at all three participating centers. The secondary outcome measure for objective (e), for example, the concentrations of the indicated laboratory parameters in both groups, UCR and UTR, at time zero and at the end of study phase 1, will be compared against the conventional hemodialysis group, and afterward against one another, using the two-sided Student’s *t* test. The individual change in these parameters, from time zero to the end of study phase 1, will be compared likewise.

(e). To assess if stricter volume control in fluid-overloaded patients (using UCR, UTR or conventional hemodialysis) affects the concentration of various proteins that might serve as novel biomarkers (including high-density lipoprotein (HDL)-associated surfactant protein B; HDL-associated serum amyloid A; HDL-associated apoC-II; plasma tryptophan; plasma choline; plasma trimethylamine-N-oxide; and plasma endotoxin). We have recently discovered that various proteins, including those mentioned here above, may render HDL dysfunctional, in hemodialysis patients [44]. Especially with surfactant, we suspect an association with fluid overload. Moreover, plasma tryptophan, plasma choline, and plasma trimethylamine-N-oxide are markers of end-stage renal disease [45]. Since one or several of these proteins or molecules might serve as novel biomarkers, we would like to use the context of the present trial to establish diagnostic assays and analyze potential changes in the serum concentration of these proteins, before and after fluid removal. Endotoxin, found in the cell membranes of gram-negative bacteria, is a biomarker representing the gut flora. Endotoxin has been shown to be associated with inflammation, nutritional status and even mortality in hemodialysis patients [46]. An incremental rise in endotoxin levels has been shown along with the progression of chronic kidney disease, and especially initiation of hemodialysis [47]. It has been suggested that hemodialysis patients might have high endotoxin levels in the blood due to repeated bacterial translocation from the gut during hemodialysis, secondary to intradialytic changes in blood pressure and/or tissue perfusion. An association with chronic fluid overload has not yet been established, but might be suspected, as a consequence of higher ultrafiltration rates and thus decreased intradialytic stability. Here, we will measure endotoxin levels with an amebocyte limulus assay in all study patients, at time zero and at the end of study phase 1. The secondary outcome measure for objective (f), for example HDL-associated serum amyloid A in both groups, UCR and UTR, at time zero and at the end of study phase 1, will be compared against the conventional hemodialysis group, and afterward against one another, using the two-sided Student’s *t* test. The individual change in these parameters, from time zero to the end of study phase 1, will be compared likewise. The results of this secondary endpoint analysis will be published separately from the clinical results of the present study.

(f). To assess if stricter volume control in fluid-overloaded patients (using UCR, UTR or conventional hemodialysis) affects quality of life measures. The secondary outcome measures for objective (g) are the mental component summary (MCS) and physical component summary (PCS) derived from the Kidney Disease Quality of Life Short Form (KDQOL-SF^TM^) [48]. The scale of both summary scores is 0 to 100 (higher indicating better quality of life). MCS and PCS in both groups, UCR and UTR, at time zero and at the end of study phase 1, will be compared against the conventional hemodialysis group, and afterward against one another, using the two-sided Student’s *t* test. The individual change in these parameters, from time zero to the end of study phase 1, will be compared likewise.

(g). To demonstrate superiority of UCR and/or UTR over conventional hemodialysis in reducing dialysis complications when previously fluid-overloaded patients are entering phase 2 and phase 3 of the presented study. In study phases 2 and 3, patients either have to reduce their dry weight further, or else have to maintain their newly reached dry weight. The secondary outcome measures for objective (h) are potentially all of the items described here above, and will be compared against the conventional hemodialysis group, and afterward against one another, in the same fashion as described here above.

(h). To assess which hemodialysis treatment modality will be chosen by the patients at the end of the study. The choice of treatment will be compared as follows: (1) number of patients choosing UCR treatment against number of patients choosing conventional treatment; (2) number of patients choosing UTR treatment against number of patients choosing conventional treatment; (3) number of patients choosing UCR treatment against number of patients choosing UTR treatment. The statistical test for analyses (1), (2) and (3) will be the two-sided chi square test, for each analysis.

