**Figure 1 F1:**
[figure not shown]
**Study flow chart.** The duration of the crossover period will depend on the run-in phase required for the next study arm: up to six hemodialysis sessions for regulation of ultrafiltration and temperature (UTR), and up to twelve hemodialysis sessions for regulation of ultrafiltration and dialysate conductivity (UCR), no run-in required for conventional hemodialysis. BCM, body composition monitor; ECW, extracellular water.

For patients who are willing to participate in the study, dry weight reduction is prescribed according to a previously published algorithm [11] described here below. Block randomization takes place in a 1:1:1 ratio into study group A (UCR), study group B (UTR) or study group C (conventional hemodialysis). The randomization code is developed using an internet-based randomization tool [51] and is not revealed to participants or investigators. We are stratifying by hemodialysis center, thus there is a different randomization list for each center.

UCR and UTR cannot be applied without previous knowledge of a particular patient’s blood volume changes during the hemodialysis session, which have been shown to be variable, intra- and inter-individually [25]. Therefore, UCR and UTR require a run-in period, which has to be performed every time that UCR and/or UTR are being used. Completion of the run-in period is judged successful for UCR, respectively UTR, if the responsible technicians from Nikkiso, respectively Fresenius, have set the blood volume corridors, respectively have determined the critical point, for adequate use of UCR, respectively UTR. No more than a maximum of twelve, respectively six, hemodialysis sessions are provided to the Nikkiso, respectively Fresenius, technicians, as previously agreed.

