### Statistical analysis plan

The statistical analysis plan (SAP) provides full details regarding the analyses, the data display, and the algorithms to be used for data derivations. The SAP includes the definition of major and minor protocol deviations, which will be identified by medically trained staff before the study closure. Safety and tolerability are analyzed descriptively. Safety analysis is performed on the intention-to-treat (ITT) population. All secondary endpoint analyses are exploratory in nature.

Sample size calculation: for the primary endpoint analysis, we will assess the differences in intradialytic complications between the three study groups, only during the first study phase. Based on a typical occurrence of 0.14 dialysis-related complications per patient-day at risk in the conventional hemodialysis group [20], two-sided testing and an expected standard deviation of 10%, an alpha = 0.05 and a beta = 0.2, a sample size of 17 patients per group was determined to detect a minimum difference of 10% between groups. The UCR and UTR groups will be tested against the conventional hemodialysis control group, and afterward against one another. We expect a drop-out rate of approximately 10%. Individuals who do not complete the study cannot be replaced, because we do not include patients with hemodialysis vintage <3 months, and all patients who qualify for the study are asked to participate after the initial BCM measurement at all three centers. Thus, the study sample was determined to consist of 60 patients with ECW ≥15%, by BCM measurement. If patients are lost to follow-up, they will be excluded from the analysis

Two different analysis sets are defined for safety and efficacy, respectively. The efficacy of UCR and UTR will be assessed in all subjects who received the study method (at least once) and did not violate the protocol in a way that might affect the evaluation of the effect of the study method on the primary objective, that is, without major protocol violations. The per-protocol set is employed in the analysis of efficacy variables. The safety analysis set includes subjects who were randomized and received at least one study method (modified intention-to-treat). The safety set is employed in the analysis of tolerability and safety variables. Statistical analysis is performed with SAS.

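### Randomisation is stratified by centre but the primary t test ignores centre, so the test is conservative and gives up some efficiency if centres differ

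*Protocol article*

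**What the plan says.** Under 'Study setting and organizational details' the article describes the allocation: "Block randomization takes place in a 1:1:1 ratio into study group A (UCR), study group B (UTR) or study group C (conventional hemodialysis"). It adds: "We are stratifying by hemodialysis center, thus there is a different randomization list for each center". There are three centres.

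Under 'Objectives and outcome measures' the primary outcome is, for each patient, the number of sessions with at least one fluid-withdrawal symptom, "divided by the number of hemodialysis sessions at risk (as by study protocol: 12 sessions per patient in study phase 1"). The test is named there: "Both groups, UCR and UTR, will be compared against the conventional hemodialysis group, and afterward against one another, using the two-sided" Student's t test.

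The sample size paragraph under 'Statistical analysis plan' is built on the same test. It gives the control rate ("Based on a typical occurrence of 0.14 dialysis-related complications per patient-day at risk in the conventional hemodialysis group"), the error rates and spread ("two-sided testing and an expected standard deviation of 10%, an alpha = 0.05 and a beta = 0.2") and the result: "a sample size of 17 patients per group was determined to detect a minimum difference of 10% between groups". With about 10% dropout the total is set at 60.

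The article uses centre in the randomisation but nowhere in a stated analysis.

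**The concern.** Separate blocked lists make the arms nearly equal in number within each centre. A centre that records many complications then contributes about equally to both arms, and its level cancels from the arm difference. The pooled SD of a plain t test does not know this: it counts the spread between centres as noise. The estimate is unaffected, but its standard error is overstated, the confidence interval is too wide and the p-value is too large.

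There are reasons to think that centre could matter here. Two of the six complication categories (the unspecified intradialytic and the patient-reported postdialysis ones) rest on a judgement of likely cause. The Discussion concedes that staff and patients are unblinded and that their judgement is subjective. Demographics for two of the three centres were not available before the start. None of this shows that the centres differ, but the sponsor itself chose centre as the stratification factor. Patients who leave cannot be replaced, so lost precision cannot be bought back by recruiting.

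**Working it through.** **Inputs from the article.** Difference 0.10, SD 0.10 (effect 0.10/0.10 = 1.0 SD), two-sided alpha 0.05, power 80%, 17 per group, about 10% dropout, 60 patients in three arms, control rate 0.14, 12 sessions per patient.

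**1. The plan's own figure.** The two-sample noncentral-t calculation gives n = 16.71, so 17 per group, as stated. The normal approximation gives 16. Allowing for dropout, 17/(1 − 0.10) = 18.9, so 19 per arm and 57 in total, which 60 covers. Power of the plain t test is 80.7% at 17, 83.0% at 18 and 86.9% at 20 per arm. The target is met.

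**2. What stratification changes.** Let R² be the share of outcome variance due to centre, with total SD σ held at 0.10. With arms balanced within centre:
- true variance of the arm difference: 2σ²(1 − R²)/n
- variance that the t test works with: about 2σ²/n
- ratio of standard errors, plain to adjusted: 1/√(1 − R²)

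The ratio is 1.03, 1.05, 1.12 and 1.20 for R² of 0.05, 0.10, 0.20 and 0.30.

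**3. Effect on error and power.** The article gives no R², so a range is assumed. Simulated results for 18 per arm (20 × 0.90 after dropout), effect 1.0 SD, with the adjusted model fitted to the two arms compared on 2n − 4 = 32 degrees of freedom:

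| Assumed R² | Type I error, plain | Power, plain | Power with centre | Gain (points) |
|---|---|---|---|---|
| 0.05 | 4.5% | 83.6% | 84.7% | 1.1 |
| 0.10 | 3.7% | 84.0% | 86.4% | 2.4 |
| 0.20 | 3.0% | 85.4% | 90.4% | 5.0 |
| 0.30 | 1.8% | 86.9% | 93.6% | 6.7 |

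At R² = 0 the noncentral-t powers are 83.0% plain and 82.9% adjusted, so adjustment costs 0.1 point. The noncentral-t powers of the adjusted model at 18 per arm (84.7, 86.6, 90.2 and 93.5%) agree with the simulation. In simulations at 17 and 20 per arm the adjusted model's type I error stayed between 4.9% and 5.2%.

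**4. How large can R² be?** Binomial noise alone, with 12 sessions at a rate of 0.14, gives √(0.14 × 0.86/12) = 0.100, which is the whole planned SD. Suppose patients within a centre did not differ at all and the three centre rates were equally spaced around 0.14, d apart. Between-centre variance is then b = 2d²/3 and mean within-centre variance is (0.1204 − b)/12. Solving b/(b + within) = R² gives:
- R² = 0.10: d = 0.041, rates about 0.10, 0.14, 0.18
- R² = 0.20: d = 0.061, rates about 0.08, 0.14, 0.20
- R² = 0.30: d = 0.079, rates about 0.06, 0.14, 0.22

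Real differences between patients would require wider spreads still. The lower part of the range is the more plausible.

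**5. Should all three arms share one variance?** Under the planned alternative (0.14 against 0.04) the binomial variances are 0.14 × 0.86/12 = 0.0100 and 0.04 × 0.96/12 = 0.0032. Simulating 12-session binomial outcomes with a single variance pooled over three arms:
- only UCR works: type I error for UTR against conventional is about 8.4%
- both work: type I error for UCR against UTR is about 1.1%

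The plain two-arm t test stays close to 5% in both cases.

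**The case against.** The strongest reply is that nothing is broken. The sample size was computed for the plain t test, reproduces and reaches its power. What is lost is only a bonus, and that bonus is nil if centre is not prognostic. This stands, and it limits the point to efficiency.

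A reader might infer that the trial is underpowered, or that 17 per group is wrong. Neither follows: on the plan's own inputs the plain test has at least 80% power, and its power rises slightly as R² grows with total SD fixed. A reader might also infer a false-positive risk; the error goes the other way.

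Second, a centre share of 20 to 30% has no support in the article and fits poorly with an SD of 0.10 that binomial noise already fills. This also stands. The article says that recording is subjective and that two centres' demographics are unknown, not that centres differ.

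Third, it is tempting to fault each t test for taking its variance from only two arms and to prefer one common-variance model for all three. The check in step 5 speaks against that: for this bounded outcome, the two-arm variance is the safer choice.

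Last, the separate analysis plan is not shown and may include an adjusted analysis. But the article does not leave the primary test open. It names a test without a centre term, so the remark concerns a stated choice and not an omitted detail.

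**Conclusion.** The point holds as a modest one about efficiency. The design balances on centre and the named primary test ignores it, so the standard error is too large and the test conservative to the extent that centre is prognostic. At 18 per arm and an effect of 1.0 SD the forgone power is about 0 to 2 points for a centre share of 0 to 10%, and about 5 to 7 points for 20 to 30%. This rests on an assumed range for that share, on near-perfect balance within centre and, for the power figures, on approximately normal outcomes. The smaller losses are the more likely. The treatment estimate is unbiased, type I error is not inflated, and the stated sample size and power need no correction. The change is worth making because it is almost free; leaving it out would not invalidate the trial.

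**What to change.** For each of the three pairwise comparisons, replace the t test by a linear model of the per-patient proportion of sessions with complications on arm and centre, fitted to the two arms compared. Report the adjusted difference with its 95% CI, and name this as the primary analysis before outcomes are examined by arm. If all three arms are modelled together, use arm-specific or robust variances instead of one pooled variance.

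The cost is a change of wording in the article's analysis statement and in the analysis plan, plus about 2 degrees of freedom (2n − 4 instead of 2n − 2), or 0.1 power point at 18 per arm if centre turns out not to matter. Centre is already known for every patient, and the sample size stays as it is.
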